### Statistical analysis

#### Sample size

We assumed that the diagnostic yield of malignancy for EUS-FNA was 80 % [23] versus 93 % for EUS-FNB [11, 13]. Because approximately 70 % of patients are expected to be diagnosed with malignancy [9], the sample size should be 342, with a power of 85 % and a two-sided significance level of 5 %. Considering 20 % of patients will be lost to follow-up, the estimated patient number in this trial should be 408.

#### Data analysis

A two-tailed distribution will be used and a *P*-value < 0.05 is considered statistically significant. Continuous variables will be measured as mean (range) and standard deviation using *t* tests or Wilcoxon rank-sum tests. Categorical variables will be measured as the count and percentage using the χ2 test. The diagnostic yield will be described as a proportion using the χ2 test; the blood contamination and cellularity in specimens with slow-pull and suction will be divided into three levels (Grade A, Grade B, and Grade C), and McNemar’s test for correlated proportions will be used. All analyses will be performed with SAS version 9.2.

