### Objectives

The primary objective of this study is to compare EUS-FNA versus EUS-FNB for the diagnostic yield (%) of malignancy [13]. The secondary objectives are to compare EUS-FNA versus EUS-FNB for 1) the overall diagnostic yield (%) from solid lesions; 2) the diagnostic yield (%) from pancreatic and nonpancreatic solid lesions, 3) the crossover diagnostic yield (%), and 4) the sample quality obtained by either the slow-pull or suction approaches, respectively.

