### Setting

A total of 408 patients will be recruited from five endoscopic centers, including Tongji Hospital, Tongji Medical College, HUST, Wuhan; Cancer Institute & Hospital, Chinese Academy of Medical Sciences, Peking Union Medical College, Beijing; Fudan University Shanghai Cancer Center, Shanghai Medical College, Fudan University, Shanghai; Sun Yat-sen University Cancer Center, Guangzhou; and the First Affiliated Hospital, College of Medicine, Zhejiang University, Hangzhou. All clinic sites meet the following criteria: (1) at least 48 patients can be recruited per site; (2) at least 2 to 4 trained physician(s) and nurse practitioner(s) per center can participate in the trial; and 3) the site agrees to strictly abide by the study protocol.

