### Randomization and blinding

The randomization will be conducted at the study office at the School of Public Health, Tongji Medical College, HUST. A stratified block randomization will be used, and the block size is 8. The patients will be allocated randomly to either group A (EUS-FNA) or group B (EUS-FNB) (1:1).

A data manager, who will not be involved in the data analysis or patient enrollment, will generate the randomization schedule. To ensure allocation concealment, the randomization schedule will be sealed under scratch cards (001–408). The scratch cards will not be opened until the baseline assessment is completed and the patient has consented to participate in the study.

The randomization schedule will not be available to the study recruiters or echoendoscopists until the baseline assessment is completed. Only the study coordinators have access to the randomization schedule. The cytologists and pathologists will be blinded during the entire study.

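### Randomisation is stratified by an unnamed factor, but the primary test is an unstratified χ2: valid, slightly conservative if the strata predict yield, and almost free to improve

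*Protocol article*

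**What the plan says.** On allocation, Randomization and blinding in the protocol article states: "A stratified block randomization will be used, and the block size is 8". The ratio is 1:1, and "the randomization schedule will be sealed under scratch cards (001–408". The factor that defines the strata is not given there or anywhere else in the article. Setting says that "A total of 408 patients will be recruited from five endoscopic centers", each able to supply at least 48, but does not say that centre is a stratum.

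On analysis, Objectives states: "The primary objective of this study is to compare EUS-FNA versus EUS-FNB for the diagnostic yield (%) of malignancy". Data analysis names the test for that outcome: "The diagnostic yield will be described as a proportion using the χ2 test". Testing is two-sided at 5 %. The section mentions no stratified test, centre term or other adjustment.

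**The concern.** Stratified blocks force the arms to be nearly equal in size within each stratum, so differences between strata largely cancel out of the treatment comparison. A plain χ2 test does not use this. Its variance comes from the pooled proportion and so still contains the between-stratum differences. If yield varies by stratum, that variance is too large, the P-value is on average too big, and some of the power that the design provides is lost. An interval built on the same variance is too wide.

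The article fixes the test for diagnostic yield, so this is a stated choice that does not use the stated design, not a detail left open. Efficiency is at stake, not validity.

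**Working it through.** **Inputs from Sample size in the protocol article.** Yield of malignancy 80 % (FNA) and 93 % (FNB); 70 % of patients malignant; power 85 %; two-sided 5 %; 342 evaluable and 408 enrolled, with 20 % loss.

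**Assumed, because the article gives no figure.** Centre is the stratum; the five centres are of equal size; the malignant patients split exactly 1:1 within each centre; the between-centre SD of yield on the logit scale runs from 0 to 1.0.

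**1. The plan's own figure.** With unpooled variance, n per arm = (1.960 + 1.036)² × (0.80 × 0.20 + 0.93 × 0.07) / 0.13² = 8.978 × 0.2251 / 0.0169 = 119.6 malignant patients. Then 2 × 119.6 / 0.70 = 341.7, which rounds up to 342. The stated 342 is therefore the size for a simple, unstratified comparison of two proportions.

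**2. Power and type I error at the planned size.** The simulation had 240 malignant patients, 120 per arm and 24 per arm per centre, with 40,000 runs per setting. Intercepts were set so that the average yields are 80 % and 93 %. For type I error, both arms have an average yield of 86.5 %.

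| Centre SD (logit) | FNA yield across centres | Power, χ2 | Power, CMH | Difference (points) | Type I error, χ2 |
|---|---|---|---|---|---|
| 0 | 80 % in all | 85.8 % | 85.6 % | -0.2 | 5.0 % |
| 0.25 | 74-85 % | 85.8 % | 85.9 % | +0.1 | 4.8 % |
| 0.5 | 67-90 % | 86.0 % | 86.6 % | +0.6 | 4.5 % |
| 0.75 | 61-93 % | 86.2 % | 87.4 % | +1.2 to +1.3 | 4.3 % |
| 1.0 | 55-96 % | 86.9 % | 89.0 % | +2.1 | 3.8 % |

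The CMH type I error stays at about 4.9 % throughout.

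**3. The same comparison at a smaller size.** If 20 % of 408 are lost, 408 × 0.80 × 0.70 / 2 = 114 malignant patients per arm remain; 115 were used so that five centres divide evenly. With 100,000 runs, χ2 against CMH gives 83.9 % vs 84.0 % at SD 0, 84.1 % vs 84.8 % at SD 0.5 and 84.8 % vs 86.7 % at SD 1.0. The differences are +0.1, +0.7 and +1.9 points. A smaller set of 8,000 runs at SD 0 gave 84.3 % vs 84.0 %, or -0.3 points, the largest loss seen.

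**4. Hand check of the type I error at SD 1.0.** With no treatment effect, the centre yields that average 86.5 % are 0.676, 0.832, 0.900, 0.942 and 0.975.
- Mean within-centre variance: (0.219 + 0.140 + 0.090 + 0.055 + 0.024) / 5 = 0.1056.
- Variance used by the χ2 test: 0.865 × 0.135 = 0.1168.
- Ratio: 0.1056 / 0.1168 = 0.904, with square root 0.951.
- The nominal cut-off of 1.96 therefore acts as 1.96 / 0.951 = 2.06, a two-sided error of about 3.9 %. This agrees with the simulated 3.8 %.

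**The case against.** The strongest reply is that nothing here is wrong. The χ2 test keeps its type I error at or below 5 %, and the sample size was computed for exactly that test, so the two agree. The stratification factor is not named and the allocation uses one card series, so any loss tied to centre is a conjecture. The protocol also works to keep centres alike: one needle type per arm, four passes by a fixed technique, standard specimen preparation, and blinded rereading of all samples by experts from two hospitals. A stratified or centre-adjusted analysis may stand in a statistical analysis plan that is not shown.

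Most of this stands, and it limits the point to a minor one. It does not remove it. The article names the test for the primary outcome, and that test leaves out the strata. Central rereading cannot remove differences in how lesions are sampled or in which lesions are sampled.

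A reader might infer more than the document supports:
- **Large centre differences.** The 52 % to 94 % accuracy range in Background is a range over published studies, not over these five centres. The lack of onsite cytology applies to the whole trial and does not separate centres.
- **A cause of insufficient power.** With 20 % loss, 408 enrolled leaves about 326, fewer than 342. That follows from the attrition arithmetic and is a separate matter from the choice of test.
- **A benefit from correcting imbalance.** Malignancy is established after randomisation, so the malignant patients need not be balanced within strata. The simulations held them balanced, so no figure supports a gain on this count.

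**Conclusion.** The point holds as a minor inefficiency. Allocation is stratified, the primary test is not, and the test is conservative to the extent that the strata predict yield. If centre is the stratum, the change in power from a stratified test is about -0.3 to +0.7 points for SD up to 0.5 and about +2 points at SD 1.0. At SD 1.0 the type I error of the χ2 test is about 3.8 % instead of 5 %. The direction follows from the design alone. The size rests on the assumed factor, equal centres and assumed spread. A significant result from the planned test would still be sound, and the 342 is unaffected.

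**What to change.** In Randomization and blinding, name the stratification factor or factors. In Data analysis, make the primary test of the diagnostic yield of malignancy a Cochran-Mantel-Haenszel test stratified by those same factors, reported with a Mantel-Haenszel risk difference and 95 % CI. Keep the plain χ2 test as a supportive analysis, and treat the overall yield in the same way. If the unstratified test is kept as primary, give the reason.

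The cost is a sentence or two and the CMH option in the SAS release already planned. No added patients or data are needed, provided that each patient's stratum was recorded. If the strata turn out not to matter, the loss is at most about 0.3 points of power. The change should be dated before outcomes by group are known. Trial status reports 372 of 408 enrolled, and the central reassessment of samples begins only after recruitment is complete, so the article's own timetable left room for it.

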**Methods/design:**

A total of 408 patients will be enrolled from five endoscopic centers. Patients will be divided into two groups: (1) group A, which is the EUS regular needle group (EUS-FNA) and (2) group B, which is the EUS ProCore needle group (EUS-FNB). Patients in group A will be examined with a 22G EchoTip Ultra needle, and patients in group B, with a 22G EchoTip ProCore needle. For all included patients, four EUS-guided passes will be made in each lesion. In the first and second pass, a slow-pull suction method of the stylet will be done. The third and fourth pass will use manual suction of 5 cc. The primary objective is to compare the diagnostic yield of malignancy by EUS-FNA versus EUS-FNB.

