### Interventions

Patients will be allocated randomly into group A (EUS-FNA, n = 204) or group B (EUS-FNB, n = 204). Group A patients will be examined with the 22G EchoTip Ultra needle, and group B will be examined with the 22G EchoTip ProCore needle.

The procedure will be performed under deep sedation according to the principles of “monitored anesthesia care.” The patients will be anesthetized with intravenous administration of propofol by trained anesthetists. All patients will receive oxygen during the procedures; blood pressure and heart rate will be monitored. Once the lesion is evaluated by EUS, the echoendoscopist will select the shortest pathway, while avoiding blood vessels, to reach the lesion. Under real-time visualization, each lesion will be punctured with four needle passes. To eliminate technical biases, the same procedure for obtaining samples will be applied to each patient undergoing EUS-FNA or EUS-FNB.

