### Technique for EUS-FNA and EUS-FNB

**1) The first and second needle passes (slow pull)** [20]: The needle will be advanced into the lesion under real-time EUS visualization. Back and forth movements will be made 20 times within the lesion and will be performed using simultaneous minimal negative pressure by pulling the needle stylet slowly and continuously.

**2) The third and fourth needle passes (5-ml suction)** [18]: After the needle has been advanced into the lesion under real-time EUS visualization, the stylet will be removed. Continuous suction will be applied with a 5-ml syringe, and the needle will be moved back and forth 20 times within the lesion. Suction will be released, and then, the needle will be withdrawn from the lesion.

After biopsy, the samples will be labeled immediately with numbers in the order of the needle pass. Samples will be prepared for histological and cytological examinations. The cytologists and pathologists will always be blinded regarding which technique was used for which specimen.

After the selected lesion has been punctured during the four needle passes, if no core tissue is obtained or if the operators determine the specimens are insufficient according to the results of the macroscopic onsite evaluation (MOSE) [21], the operators will use a proper puncture method to obtain samples as the backup procedure.

If diagnostic failure occurs, the patient will crossover to the other arm after agreeing to accept a needle biopsy again on the same lesion 1 week later with the same method mentioned above.

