### Assessment standards

After patient recruitment is completed, all samples will be reassessed by selected cytologists and pathologists from Tongji Hospital, Tongji Medical College, HUST, and from the Cancer Institute & Hospital, Chinese Academy of Medical Sciences, Peking Union Medical College. They will assess the samples following the protocol and remain blinded regarding which technique was used for which specimen. Each sample will be assessed by two independent experts. If the two experts have different judgments, they should discuss it together and make a final decision [7].

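### McNemar's test does not fit the slow-pull versus suction data: each lesion gives two three-level grades per technique, and the test takes one binary pair per lesion

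*Protocol article*

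**What the plan says.** All references are to the protocol article.

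- **Design.** Under Interventions, "each lesion will be punctured with four needle passes". Under Technique for EUS-FNA and EUS-FNB, passes 1 and 2 are slow-pull and passes 3 and 4 use 5-ml suction.
- **Samples.** The same section says that "the samples will be labeled immediately with numbers in the order of the needle pass". Under Assessment standards, "Each sample will be assessed by two independent experts", and the experts settle disagreements by discussion. Each lesion can therefore have two final grades per technique on each scale.
- **Scale.** The histology and cytology criteria grade blood contamination and cellularity as A, B or C.
- **Analysis.** Under Data analysis, "the blood contamination and cellularity in specimens with slow-pull and suction will be divided into three levels", and "McNemar’s test for correlated proportions will be used". The significance level is 5 %, two-sided.
- **Status.** Sample quality by slow-pull or suction is the fourth secondary objective. The Discussion hopes that it will give a clear conclusion on which sampling method to use for which procedure.

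**The concern.** McNemar's test compares two binary readings on each of a set of independent units. Here each lesion has four readings, two per technique, on a three-level scale. The plan gives no rule for getting from one to the other, and it names specimens, not lesions or patients, as what is compared.

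There are three ways to make the test run:

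1. Pair specimens across techniques (1 with 3 and 2 with 4, or 1 with 4 and 2 with 3) and count every pair. Two pairs then come from one lesion.
2. Use one pass per technique and drop half the readings. The result then depends on which pass is chosen.
3. Collapse the two readings to one grade per technique, such as the better one, and split it into two categories. Ordinal information is lost.

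The first can be over-confident. The other two keep the 5 % level but waste data. At stake is the reliability of a recommendation on sampling method that the Discussion hopes to make.

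**Working it through.** **Inputs from the article.** Four passes per lesion, two per technique; three grades; two-sided 5 %; 408 patients, 204 per arm. The article gives no sample size, power or within-lesion correlation for this comparison, so it has no figure of its own to reproduce. Its evaluable sample size for the primary endpoint does reproduce: (1.960 + 1.036)² × (0.80 × 0.20 + 0.93 × 0.07) / 0.13² = 119.59 per arm, and 2 × 119.59 / 0.70 = 341.7, hence 342. Nothing below touches it.

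**Assumptions (not in the article).** One lesion per patient; grades A/B/C in 45/30/25 % of samples; an underlying normal scale with 30 % of variance due to lesion and 0-30 % due to lesion-by-technique; a technique shift of 0.2 SD for power.

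**Step 1: error if all specimen pairs are counted as independent.** There would be 2 × 408 = 816 pairs. Let D₁ and D₂ be the two slow-pull minus suction differences in one lesion, each with variance v, and ρ their correlation. Over N lesions the sum of differences has variance 2Nv(1 + ρ), while McNemar's test assumes 2Nv. The true two-sided error is therefore

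2 × [1 − Φ(1.96 / √(1 + ρ))].

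| ρ | True error |
|---|---|
| 0 | 5.0 % |
| 0.1 | 6.2 % |
| 0.2 | 7.4 % |
| 0.3 | 8.6 % |
| 0.4 | 9.8 % |
| 1.0 | 16.6 % |

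For example, at ρ = 0.2, 1.96 / √1.2 = 1.789, which gives 7.4 %.

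**Step 2: what makes ρ positive.** A lesion effect shared by all four passes cancels in the differences and leaves ρ = 0. Only a lesion-by-technique effect, where some lesions suit one technique better, makes ρ positive. Simulation with a binary grade and 408 lesions (4,000 runs per setting) agrees:

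| Lesion-by-technique variance | Resulting ρ | Error, all specimen pairs |
|---|---|---|
| none | about 0 | 4.7-5.2 % |
| 10 % | 0.08 | 5.7-6.3 % |
| 20 % | 0.17 | 7.4-7.5 % |
| 30 % | 0.26-0.27 | 7.8-8.1 % |

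With the 45/30/25 % grades, the simulated error was about 7 % at 20 % and 7.8-8.7 % at 30 %. One pair per lesion, or a lesion-clustered variance, stayed at about 4.5-5.7 % in every setting.

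**Step 3: power if each lesion gives one pair.** With 204 lesions (one arm), a 0.2 SD shift and lesion-by-technique variance from 0 to 30 %:

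| Analysis | Power |
|---|---|
| McNemar, one pass per technique, grade A against B/C | about 42 % |
| McNemar, better grade per technique | 50-56 % |
| Paired rank test on averaged grades, all four readings | 70-81 % |

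All three hold the 5 % level. With both arms pooled (408 lesions) every power is higher and the gaps are smaller, but the order is the same.

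**The case against.** **The plan does not say that specimen pairs are treated as independent.** This stands. A reader might infer from the word specimens that 816 pairs will enter the test. No section says so, and no section matches pass 1 with pass 3. The wording is equally compatible with one combined grade per technique per lesion, and the Discussion describes both methods as used on each lesion. Step 1 is therefore conditional.

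**How replicate passes are reduced is detail for the full protocol or the analysis plan, which are not shown.** This stands in part. Silence on that rule alone would be no finding. But the article itself fixes the test, and a binary one-pair test fits these data only after readings or grade levels are thrown away. Reading the test as its extension to three categories (a test of symmetry) would deal with the scale, but not with two readings per technique.

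**A better or consensus grade over two passes is valid and uses both readings.** It is valid. In the setting of Step 3, though, McNemar's test on the better grade had 50-56 % power, against 70-81 % for the ordinal lesion-level analysis.

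**The inflation is small and assumed.** A reader might infer that the error rate nearly doubles. That needs ρ of about 0.35-0.40 (9.2-9.8 %), and the documents give no ρ. Ordinary lesion-to-lesion variation causes no inflation at all.

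**It is the last of four secondary objectives.** True, and it limits the weight of the point.

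**Conclusion.** The point holds in a limited form. The prescribed test does not match the data structure: two three-level grades per technique per lesion, against one binary pair per independent unit. The consequence depends on a step that the article does not state. Counting all specimen pairs as independent gives an error of about 7-9 % if 20-30 % of variance is lesion-by-technique, and 5 % if there is none. Reducing to one pass or one collapsed grade keeps 5 % but gives about 42-56 % power where 70-81 % is available, at an assumed 0.2 SD shift and 204 lesions. The loss of power does not require a lesion-by-technique effect.

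The documents do not support the claim that pairs will in fact be counted as independent, or that the error will nearly double. The primary comparison and the sample size are unaffected. The change is still worth making, because the Discussion hopes to base a method recommendation on this result.

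**What to change.** In Data analysis, replace McNemar's test for the slow-pull versus suction comparison with an analysis that has the lesion as the unit and uses all four ordinal grades. Suggested wording:

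> For blood contamination and cellularity, grades A, B and C are scored 1, 2 and 3. The two slow-pull scores and the two suction scores of each lesion are averaged, and the within-lesion difference is tested with a two-sided Wilcoxon signed-rank test at 5 %. The number of lesions is the sample size.

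A cumulative-logit model with lesion-clustered variance is an alternative, not an equivalent. It estimates a population-averaged odds ratio under proportional odds, while the rank test addresses within-lesion differences. One of the two should be named in advance.

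**Cost.** One sentence and no new data. Averaging treats the three grades as equally spaced, and the nominal n is up to 408 lesions rather than 816 specimen pairs. Under Assessment standards, the reassessment follows the end of recruitment. Trial status reports 372 patients enrolled and recruitment still open, so at that date the rule could be set before those grades existed.

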#### Histology assessment criteria

The histological assessment will involve the following:Tissue integrity assessment [20, 22]Grade A: core tissue (an architecturally intact piece of tissue measuring at least 550 micron in greatest axis, as the diameter of a high-power microscopic field), clearly characterizes the lesion sufficient for diagnosisGrade B: core fragments present, tissue does not meet the criteria for architecturally intact histology but can still yield a diagnosis based on cell morphologyGrade C: no lesion tissue found and cannot yield a diagnosisBlood cell contamination assessment [18]Grade A: little blood contamination, minimal surface area (SA) < 25 % of slideGrade B: medium blood contamination, 25–50 % of the slideGrade C: much blood contamination, SA > 50 % of the slide

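### McNemar's test is assigned to three-level grades from two slow-pull and two suction passes per patient, and it addresses a different contrast from the one worded in secondary objective 4

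*Protocol article*

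**What the plan says.** Four places in the protocol article bear on this point.

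- **Data analysis.** The sample-quality sentence concerns "the blood contamination and cellularity in specimens with slow-pull and suction". These outcomes "will be divided into three levels (Grade A, Grade B, and Grade C"), and "McNemar’s test for correlated proportions will be used". An earlier sentence in the same section assigns the chi-square test to categorical variables in general.
- **Objectives.** The list opens with "The secondary objectives are to compare EUS-FNA versus EUS-FNB for", and its fourth item is "the sample quality obtained by either the slow-pull or suction approaches, respectively".
- **Interventions, and Technique for EUS-FNA and EUS-FNB.** Under real-time imaging "each lesion will be punctured with four needle passes". The first two passes use slow-pull and the last two use 5-ml suction. Samples are labelled by pass.
- **Histology and Cytology assessment criteria.** Each quality outcome has grades A, B and C in order of quality. The histology list starts with "Tissue integrity assessment", which the McNemar sentence does not mention.

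The Background and the Discussion also state an interest in slow-pull versus suction. The Discussion hopes to say which sampling method suits which procedure.

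**The concern.** McNemar's test compares two correlated proportions using one yes/no pair per independent unit. The article assigns it to outcomes with three ordered grades and two observations per technique per patient. To run it, someone must choose a cut-point (A versus B/C, or A/B versus C) or move to a 3×3 paired test, and must also reduce two-plus-two passes to one pair. The article fixes the scale and the test together but does not connect them.

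The second difficulty is the contrast. FNA and FNB patients are separate randomized groups, so a within-patient test of slow-pull against suction does not answer an FNA-versus-FNB question.

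If this stays as it is, the sample-quality result may depend on an unstated choice, and the contrast worded in objective 4 has no test explicitly linked to it.

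**Working it through.** **The plan's own figure.** The article gives no number for this analysis. Its sample size belongs to the primary endpoint and reproduces: (1.960 + 1.036)² × (0.80×0.20 + 0.93×0.07) / 0.13² = 119.6 malignant cases per arm, and 2 × 119.6 / 0.70 = 341.7, so 342. Nothing below changes it.

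**Step 1: test against data.**

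| | McNemar's test needs | The article provides |
|---|---|---|
| Outcome | two categories | three ordered grades |
| Observations per patient | one pair | two slow-pull and two suction passes |
| Contrast | within patient | objective 4: between randomized arms, 204 versus 204 |

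**Step 2: does the cut-point matter?** Take a constructed table of 408 pairs (rows one technique, columns the other; grades A, B, C): 100, 40, 5 / 40, 100, 8 / 5, 25, 85. McNemar's statistic is (b − c)²/(b + c).

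- A versus B/C: b = 40 + 5 = 45 and c = 40 + 5 = 45. The statistic is 0 and p = 1.00.
- A/B versus C: b = 5 + 8 = 13 and c = 5 + 25 = 30. The statistic is 17²/43 = 6.72 and p = 0.0095.
- Bowker's 3×3 test on the same table: 0²/80 + 0²/10 + 17²/33 = 8.76 on 3 degrees of freedom, p = 0.033.

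The same data give opposite conclusions at the two cut-points. The table shows what can happen; it does not show how often.

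**Step 3: does the handling of passes matter?** A simulation used 408 patients, two passes per technique, no true technique effect, grade shares of 40/35/25 % and a between-patient share of latent variance of 0.3. All of these except the patient and pass counts are assumptions. Each setting had 3,000 simulated trials, so the simulation standard error near 0.05 is √(0.05 × 0.95 / 3,000) = 0.004.

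| Patient-by-technique variance share | Type I error, both pass pairs treated as independent (A versus B/C) | Type I error, one binary result per technique per patient |
|---|---|---|
| 0 | 0.057 | 0.047 |
| 0.1 | 0.059 | 0.055 |
| 0.2 | 0.076 | 0.058 |
| 0.3 | 0.080 | 0.050 |
| 0.4 | 0.094 | 0.048 |

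At a share of zero no inflation is expected, because the patient effect cancels within each pair; 0.057 is within simulation error of 0.05. Inflation appears as patients differ in how they respond to technique. Bowker's test on the same unreduced pairs ran from about 0.05 to 0.09, so moving to three categories does not cure the clustering.

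**Step 4: efficiency, for illustration only.** Assume 326 patients (408 × 0.8), a patient standard deviation of 1 logit and an odds ratio of 1.5 for a worse grade with suction. Approximate power is:

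- McNemar on one pass pair: 58–61 %
- an ordinal paired test on that same pair: 75 %
- McNemar on the better of two passes (A versus B/C): 80 %
- an ordinal paired test on all four passes: 95–96 %

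For one-pair McNemar the two cut-points disagreed on significance in 31–37 % of trials at odds ratios of 1.3 to 1.5, and in 6 % at 2.0.

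**The case against.** The strongest reply is that the sentence is loose but workable. A paired test is the right family for slow-pull versus suction, and that comparison is an aim in the Background and the Discussion. McNemar's test has a k-category extension. Collapsing rules are often left to a full protocol or analysis plan, which is not shown here. One pair per patient holds its type I error.

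Much of this stands, and it rules out several stronger readings that a reader might infer:

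- **That objective 4 has no valid test at all.** The general chi-square sentence can cover FNA versus FNB on the grades, including tissue integrity. It is not linked to that objective, and it ignores grade order and, at pass level, clustering.
- **That tissue integrity goes unanalysed.** It is absent only from the McNemar sentence.
- **That McNemar's test cannot be run.** It can, after collapsing and reducing, or with Bowker's test on one three-level pair per patient.
- **That the choices will be made after seeing the data.** An unseen analysis plan may already settle them.
- **That the method costs a known amount of power.** The documents give no grade distribution, effect or correlation. Much of the gap in Step 4 comes from dropping two of the four passes, which the article does not prescribe. Grades come from the biopsy itself, so 326 patients also understates the data likely to be available.

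What the reply does not remove is that the article names a three-level scale and a test of correlated proportions in one sentence, for four passes per patient, and ties that test to a contrast other than the one in its objective.

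**Conclusion.** The point holds as a moderate flaw in one secondary analysis. The stated test fits the stated data only after steps that the article does not specify. The choice of cut-point can reverse significance, and ignoring the pairing of passes within patients can raise type I error to between about 0.06 and 0.09 for patient-by-technique variance shares of 0.1 to 0.4. Both illustrations rest on assumed grade distributions, and the second also on assumed correlations; the true size cannot be derived from the documents. The mismatch between the McNemar contrast and objective 4 follows from the text alone and needs no assumption.

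The primary chi-square comparison, the sample size and the data collection are unaffected, so treating this as a threat to the trial's main conclusion would go beyond what the documents support.

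**What to change.** Before the centrally reassessed grades are analysed, replace McNemar's test with a cumulative-logit model of the pass-level grades for blood contamination, cellularity and tissue integrity. Include needle, technique and needle × technique, and account for clustering by patient, either with GEE and a robust variance or with random effects. If random effects are used, add a patient-by-technique term to the patient intercept, because an intercept alone would not capture the variation that drives the inflation in Step 3. Report:

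- FNB versus FNA within slow-pull and within suction, which answers objective 4 as worded;
- slow-pull versus suction within each needle, which answers the Discussion's question;
- the interaction.

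State these contrasts in the objectives so that aim and analysis agree.

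The cost is revised wording, modest programming and a proportional-odds assumption to check. No new data are needed, since samples are already labelled by pass. The timing is feasible: Trial status reports 372 of 408 patients enrolled, and Assessment standards places the blinded reassessment after recruitment ends.
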